#### Recruitment

Around 400 men undergo RARP at our department each year. In average, we estimate 30–35 patients per month. Six months after the start of recruitment, a total of 119 patients had agreed to participate. Therefore, we expect to enroll the initially planned 300 patients within 16–18 months. Recruitment is monitored by [name] There are no financial or non-financial incentives provided to trial investigators or participants for enrollment.

#### Randomization

Eligible patients will be stratified for lymphocele risk factors and operating surgeon. Hereafter, randomization will be performed as block randomization with a 1:1 allocation to either using a PF (PELYCAN) or standard procedure without a PF (control). Block sizes will be kept confidential until study completion. Randomization and allocation will take place the day before surgery with a web-based computer algorithm (uroservy.de), which was specially developed for this study by the Heinrich-Lanz Center for Digital Health, Medical Faculty Mannheim, University of Heidelberg.

Randomization will be stratified for possible risk factors for lymphocele formation and the surgeon performing the procedure. The process of stratification is included in the “randomization process”: Patients are stratified for anticoagulation therapy (yes vs. no), extended lymphadenectomy (yes vs. no), diabetes mellitus (yes vs. no), and the surgeon performing the procedure. These categories have to be answered during the randomization process. Following this stratified proportionate sampling combined with randomization, we aim to ensure an equal allocation of participants to each experimental condition (intervention vs. non-intervention). That is done to control for the possible confounding variables regarding postoperative lymphocele formation (e.g., preventing that significantly more patients with extended LAD are randomized into the non-intervention group). Stratification based on intraoperative patient characteristics was considered impossible. To avoid over-stratification, we limited the number of strata. Aiming for a high number of patients, blocking within the strata will be performed. All patients included will be used for statistical analyses.

The randomization and allocation process will be performed by a person, who is completely uninvolved in the running of the trial, the study inclusion, the process of taking the patients’ consent, the operation or postoperative assessment of lymphoceles. This person cannot be influenced by people involved in the trial.

All randomized study participants will stay included in the trial. Follow-up information will be collected in order to prevent missing data.

Concealment is achieved by using the web-based computer algorithm mentioned above. Permuted-block randomization will be used for equal proportions regarding the provided treatment. Block sizes will be kept confidential until study completion, to ensure concealment. Only the surgical assistant is informed about the study inclusion and allocation the evening before the operation takes place. By blocking within the strata, allocation becomes even more unpredictable for the surgeon.

Whether or not the intervention has been performed is concealed by using a code, which is assigned to each patient individually. A list of patients and their matching codes is provided in a separate document. Allocation will not be released until the end of the 6-month follow-up, ensuring concealment. Enrollment will be performed by the admission doctor as mentioned above.

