##### Group A: Intervention = PELYCAN

Following, the standard operative technique is described. Small variations according to the surgeon’s preference, such as the order of the right- and left-sided lymphadenectomy or using clips during lymphadenectomy and their amount, are allowed but must be recorded in the operation protocol. Radical prostatectomy will be performed by experienced high-volume surgeons. All surgeons use the same steps for LND, RARP, and the same vesicourethral anastomosis technique. The da Vinci® Xi Surgical System is used to perform the procedures.

Patients are under general anesthesia. The patient is placed in approximately 45° Trendelenburg position. Both arms are placed along the body. In total 6 trocars are placed in a modified, semicircular fashion (Fig. 1): 4 da Vinci® trocars (supraumbilical (8 mm trocar), left and right to the umbilicus (two 8 mm trocars), lower left hemiabdomen (8 mm trocar)) and 2 assistant trocars (right lower (11 mm trocar) and right upper (5 mm trocar) abdomen). Diagnostic laparoscopy is used to identify peritoneal adhesions prior to trocar placement. Peritoneum is incised next to the medial umbilical ligament. Next, the urachus is ligated, followed by preparation of the retropubic space down to the symphysis, which fully mobilizes the urinary bladder. Lateral umbilical ligament is incised to the spermatic duct on the left side. The procedure is repeated at the contralateral side (Fig. 2b). Afterwards, pelvic lymph node dissection is performed: The right internal inguinal ring is identified, followed by preparation of the lymph-node containing tissue in the obturator fossa between the external iliac vein and the obturator nerve. If assessed necessary by the surgeon, titanium clips (AESCULAP® Challenger® Ti-P, B. Braun, Melsungen, Germany) are used. In high-risk PCa extended LND (lateral margin: external iliac artery, cranial margin: bifurcation of the iliac artery) is performed. Lymph node dissection is performed at both sides. Lymph node tissue is placed in the ExBag® (ASID BONZ, Herrenberg, Germany) specimen pouch. After incision of the endopelvic fascia, the prostate is mobilized and suture ligation of the dorsal venous plexus is performed using one 4/0 Vicryl (Ethicon Inc., Cincinnati, USA) running suture. Bladder neck preparation is done in gentle technique with anterior incision.

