**Fig. 2 Fig2:**
[figure not shown]
Intraoperative anatomy. **a** As seen from the cranial, intraperitoneal position of the camera. **b** After incision of the peritoneum along lateral umbilical fold. **c** After the PFs are created. **d** After fixation of the PFs. Asterisk indicates fixation to the pelvic floor using Vicryl 4/0 sutures; black star indicates vesicourethral anastomosis

The foley catheter can now be grabbed and moved ventrocranially. Now, the dorsal bladder neck is cut through. The anterior part of Denonvilliers’ fascia is severed, the spermatic duct and seminal vesicles identified, dissected, and held up/stretched. The anterior wall of the rectum can now be separated from the posterior part of the prostate either above or below the Denonvillier’s fascia depending on the nerve-sparing or non-nerve-sparing attempt. Depending on the preoperative agreement the neuro-vascular bundle is saved on both sides, one side or not saved in order to achieve higher oncologic safety. After apical separation, the urethra is incised and the foley catheter moved ventrally, which allows the separation of the posterior part of the urethrae. The prostate/specimen is placed in the ExBag® (Medtronic, Dublin, Ireland) specimen pouch. Bleeding is stopped using 4/0 Vicryl sutures and/or bipolar. After performing the dorsal Rocco stitch using a 3/0 V-loc™ barbed suture (Covidien, New Haven, USA), the vesicourethral anastomosis is sutured starting at 5 and 7 o’clock in lithotomy position and using a bidirectional 3/0 V-loc™ barbed suture (Covidien, New Haven, USA). Before the anastomosis is closed at 12 o’clock, a new foley catheter is inserted under visual control and the vesicourethral anastomosis is closed. Afterwards, the ventral Rocco stitch is performed. Next, the anastomosis is controlled for its integrity by filling the bladder with a minimum volume of 60 ml NaCl using the inserted catheter. Hereafter, the surgeon is informed about the result of patient randomization.

The ventral peritoneum is incised laterally on both sides to create the PF (Fig. 2c). Those PF are fixated to the pelvic floor opposite to the region of the lymphadenectomy using 2 interrupted 4/0 Vicryl (Ethicon Inc., Cincinnati, USA) sutures (Fig. 2d). Figure 3 shows intraoperative pictures of the creation and fixation of the peritoneal flap on the right side.

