#### Blinding and blinding mechanism

To reduce performance bias, patients and assessors will be blinded to group allocation until 6 months after surgery [40]. Randomization will take place 1 day before surgery. The operating surgeon will be informed about group allocation after the vesicourethral anastomosis is finished. This late point of involving the surgeon guarantees a consistent procedure and thereby minimizes the surgeon’s bias.

By using a unique randomization ID for each patient, patients, outcome-assessors for in-patient treatment and examination of lymphoceles as well as the care providers/outcome-assessors for examination and follow-up after discharge will be blinded. Data collectors will be kept blinded as well until the data collection will be finished.

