One point of discussion is that due to the nature of the intervention, a complete double-blinding in terms of blinding the surgeon is impossible. However, until the vesicourethral anastomosis is finished, the surgeon will remain blinded. This late point of unblinding guarantees a consistent procedure and thereby lowers the surgeons’ bias. Additionally, outcomes assessors will be blinded until 6 months postoperatively.

In conclusion, the PELYCAN study is a parallel-group, patient- and assessor-blinded, phase III, adaptive randomized controlled superiority trial investigating the impact of PFs on symptomatic lymphoceles following RARP with LND performed by experienced surgeons beyond the learning curve. The PELYCAN study has the potential to initiate a paradigm shift in order to avoid postoperative lymphoceles and further refine the technique of RARP.

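### The surgical assistant learns the arm the evening before surgery, so the surgeon's blinding during node dissection rests on a colleague's silence and the late reveal cannot guarantee a consistent procedure

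*Protocol article*

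**What the plan says.** Randomization takes place the day before surgery. It uses a web-based algorithm and is carried out by a person with no other part in the trial (Randomization). The same section then states who is told first: "Only the surgical assistant is informed about the study inclusion and allocation the evening before the operation takes place".

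The surgeon is told much later. In the operative description for Group A, the anastomosis is closed, the bladder is filled to check for leakage, and then: "Hereafter, the surgeon is informed about the result of patient randomization". Group B: Control sets the same moment for control patients. Blinding and blinding mechanism places it after the anastomosis is finished.

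The article draws a strong conclusion from this timing. Blinding and blinding mechanism says "This late point of involving the surgeon guarantees a consistent procedure", and the Discussion says "This late point of unblinding guarantees a consistent procedure". Both sentences go on to say that surgeon bias is thereby reduced.

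Some steps before the reveal are discretionary. During node dissection, clips are optional: "If assessed necessary by the surgeon, titanium clips" are used. After the prostate is removed, the text reads: "Bleeding is stopped using 4/0 Vicryl sutures and/or bipolar".

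**The concern.** The flap is created after the reveal, but the steps that could influence lymph leakage come before it. Keeping the surgeon unaware of the arm until the flap step is the article's stated protection against doing those earlier steps differently by arm.

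That protection has a gap. One member of the surgical team knows the arm throughout the phase that is meant to be blinded. The assistant could mention it, hint at it, or let it colour assistance during dissection. If clip use or haemostasis then differed by arm, and if that difference affected symptomatic lymphoceles, the comparison would no longer isolate the flap. The gap is avoidable, because a suitable release point for the surgeon already exists.

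**Working it through.** No arithmetic decides this point, and no stated sample size, alpha or power depends on it. The check sets the sequence of events beside the claim.

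| Order | Event | Surgeon told the arm? | Assistant told the arm? | Section |
|---|---|---|---|---|
| 1 | Consent and enrolment | No | No | Participant timeline |
| 2 | Randomization, day before surgery | No | No | Randomization |
| 3 | Disclosure to the assistant, evening before | No | **Yes** | Randomization |
| 4 | Node dissection, clips optional | No | **Yes** | Group A; Group B |
| 5 | Prostate removal, haemostasis by suture or bipolar | No | **Yes** | Group A |
| 6 | Anastomosis and leak test | No | **Yes** | Group A |
| 7 | Disclosure to the surgeon | Yes | Yes | Group A; Group B; Blinding |
| 8 | Flap created (Group A only) | Yes | Yes | Group A |

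1. **Does the guarantee follow?** It would if nobody in the operating team knew the arm in rows 4 to 6. One person does, so consistency depends on that person's conduct as well as on the timing of row 7.

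2. **Do other stated safeguards cover this route?** Confidential block sizes stop the surgeon predicting the next allocation. Individual patient codes protect the allocation during follow-up. Emergency unblinding restricts disclosure, but its setting is exceptional code breaks. None of these governs an assistant who is routinely told in advance.

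3. **Is there a stated need for early disclosure?** The only flap material described is suture: the flaps are fixed "using 2 interrupted 4/0 Vicryl" sutures. The same material is already used earlier in the operation, where "suture ligation of the dorsal venous plexus is performed using one 4/0 Vicryl" running suture. Group B has the same steps apart from the flap, so this suture is in use in both arms. The documents show no preparation that requires the assistant to know sooner.

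4. **How many patients could a change reach?** Trial status gives 140 of 300 randomized at submission on 16 August 2020, so 300 − 140 = 160 remained. Recruitment was continuing and the protocol version is dated October 2020, so 160 is an upper bound under the 300-patient plan. It would be larger only if the interim recalculation raised the target, which is capped at 1000.

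**The case against.** The strongest reply is that harm needs four things, none of which the article states: the informed assistant is at the table during dissection, the arm is passed on or acted upon, the surgeon or assistant then works differently, and that difference changes the lymphocele rate. The first is likely, given two assistant trocars and the advance notice, but it is not stated.

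The article also limits the room for a difference. All surgeons use the same dissection steps, extended dissection is tied to high-risk cancer with defined margins, and randomization is stratified by surgeon and by extended lymphadenectomy. Clip use and number must be recorded, so an imbalance would be visible. The Introduction reports no difference in lymphocele incidence between metallic clips and electrocoagulation so far, while calling those results debated. The Discussion also concedes that the surgeon cannot be fully blinded.

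All of this stands, and it keeps the point small. A fuller protocol might also instruct the assistant to stay silent, so the absence of such an instruction here is not the complaint. The complaint is about the early release that the article does fix, and the guarantee that it does assert. A silence instruction would reduce the risk but would still leave the guarantee resting on one person.

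A reader might infer more: that surgeons were in fact unblinded, that bias occurred, or that the type I error is inflated by some amount. The documents support none of these. They give no clip rate and no risk ratio showing a clip effect. They give no imbalance between arms either, so any such figure would be built on invented inputs. Nor does the point show that concealment at enrolment failed, since consent and randomization come before the assistant is told. It also does not touch the planned blinding of patients and outcome assessors.

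**Conclusion.** The point holds as a minor weakness in design. Telling the assistant the evening before makes the surgeon's blinding during dissection and discretionary clip use depend on a colleague's silence. The late reveal lowers the risk of surgeon bias, but it does not guarantee a consistent procedure.

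The size and direction of any bias are unknown and may be zero, and no quantitative error or power figure should be attached. The conclusion rests on the order of steps in the article and on one assumption: that the informed assistant takes part in the operation before the reveal.

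**What to change.** For patients not yet randomized, amend the Randomization section so that the allocation is held in the web system, or by the independent person who performs the randomization, until the leak test is complete. It is then released to surgeon and assistant at the same time.

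In Blinding and blinding mechanism and in the Discussion, replace the guarantee with a plain account of who knew the arm and when. This should include the fact that, for patients operated on before the change, the assistant knew it from the evening before.

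The cost is one amendment with ethics approval and a small logistic step, since someone must retrieve the allocation during the operation. The documents do not confirm that the web tool can already do a timed release; if it cannot, the independent person can hold the result and pass it on. Sample size, analysis and patient burden do not change.

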#### Blinding and blinding mechanism

To reduce performance bias, patients and assessors will be blinded to group allocation until 6 months after surgery [40]. Randomization will take place 1 day before surgery. The operating surgeon will be informed about group allocation after the vesicourethral anastomosis is finished. This late point of involving the surgeon guarantees a consistent procedure and thereby minimizes the surgeon’s bias.

By using a unique randomization ID for each patient, patients, outcome-assessors for in-patient treatment and examination of lymphoceles as well as the care providers/outcome-assessors for examination and follow-up after discharge will be blinded. Data collectors will be kept blinded as well until the data collection will be finished.

##### Emergency unblinding

To maintain the overall quality and legitimacy of the clinical trial, code breaks should occur only in exceptional circumstances when knowledge of the actual treatment is absolutely essential for further management of the patient. If unblinding is deemed to be necessary, the investigator should use the system for emergency unblinding through contacting the PI or the people responsible for study coordination. The investigator is encouraged to maintain blind as long as possible. The actual allocation must not be disclosed to the patient and/or other study personnel including other site personnel nor should there be any written or verbal disclosure of the code in any of the corresponding patient documents. The Investigator must report all code breaks (with reason) as they occur.

### Data collection

#### Trial procedures and evaluations

##### Primary outcome

The primary endpoint will be identified by directly asking the patient. Since a symptomatic lymphocele provides symptoms, we consider the validity and reliability of this approach as high. The same approach will be used for drainage insertion and deep vein thrombosis. Therefore, patients will be contacted and sent a questionnaire by email. If the primary endpoint was met or patients will not respond to the email, they will be contacted by another email, per letter or telephone.

To promote data quality the patients’ follow-up specialists will be contacted and asked for the occurrence of the primary endpoint. Contacting patients and their follow-up specialists will have been allowed in the written informed consent.

##### Secondary outcomes

Sonographic evaluation for lymphoceles is included in the discharge examinations. All results are noted in the discharge letter. Therefore, we have no doubt that assessing for “asymptomatic lymphocele at the day of discharge” will have high validity and reliability. The occurrence of “asymptomatic lymphocele,” “lymphedema,” “erysipelas,” and “rehospitalization” is included in the questionnaire mentioned above. Additionally, patients will receive the validated EORTC QLQ-C30 and the Lymphoedema Functioning, Disability and Health Questionnaire for Lower Limb Lymphoedema (Lymph-ICF-LL).

##### Training plans

All assessors were instructed about the necessary measures at discharge and how to document each study parameter.

#### Retention

By contacting the patients using different methods, we expect to have low rates of patients “lost to follow-up.” By asking the patients’ follow-up specialist, we create a “double measurement.” That improves retention and aims to decrease the number of patients “lost to follow-up.”

Since the intervention is an operative procedure at the beginning of the study period, non-adherence is no matter of discussion in our cohort. Once a patient is enrolled or randomized, the study site will make every reasonable effort to follow the patient for the entire study period.

##### Participant withdrawal

Participants may withdraw from the study for any reason at any time. The investigator also may withdraw participants from the study in order to protect their safety (e.g., if the planned PF is not possible due to anatomical reasons or an anesthesiologic need for finishing the procedure without artificial prolonging the operation time).

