### Statistical methods

#### Outcomes

The intervention arm (PELYCAN) will be compared against the control for all primary analyses. The primary analysis will be based on the intention-to-treat (ITT) principle. In addition, per protocol (PP) and as-treated (AT) analyses will be performed as sensitivity analysis. We will use chi-squared test for binary outcomes and *t* test for continuous outcomes. Categorical data will be reported with absolute and relative frequencies. Continuous outcomes will be reported with mean/median as well as standard deviation and (interquartile)-range. For subgroup analysis, we will use regression methods. Multivariable analyses will be based on logistic regression for binary outcomes and linear regression for continuous. *P* values will be reported to four decimal places with *p* values less than 0.001 reported as *p* < 0.001. Up-to-date versions of SPSS (Chicago, IL) and R will be used to conduct analyses. For the primary outcome, the *p* value will be adjusted according to the adaptive design in order to avoid a type I error. All other analyses will be exploratory with 2-sided *p* values of alpha < 0.05 and a power of 80%. Statistical analysis will be performed by a statistician who is otherwise not involved in the conduct of the study.

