#### Missing data

Since the intervention is an operative procedure at the beginning of the study period non-adherence is no matter of discussion in our cohort. Once a patient is enrolled or randomized, the study site will make every reasonable effort to follow the patient for the entire study period. If a patient is not willing to send back the information of the follow-up after 6 months, we will report reasons for withdrawal for each randomization group and compare the reasons qualitatively.

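### The withdrawal rule allows patients to leave the study when the planned flap cannot be made, which contradicts the promise to keep all randomised patients and can bias the primary comparison

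*Protocol article*

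**What the plan says.** The Participant withdrawal section (under Retention) allows investigator-led withdrawal on safety grounds: "The investigator also may withdraw participants from the study in order to protect their safety (e.g., if the planned PF is not possible". The sentence gives anatomical reasons for this and adds a second example: "an anesthesiologic need for finishing the procedure without artificial prolonging the operation time".

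Other sections of the same article say:

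- Randomization, on timing: "Randomization and allocation will take place the day before surgery". The surgeon learns the arm only once the vesicourethral anastomosis is finished (Blinding and blinding mechanism).
- Randomization, on retention: "All randomized study participants will stay included in the trial", and "All patients included will be used for statistical analyses".
- Statistical methods, Outcomes: "The primary analysis will be based on the intention-to-treat (ITT) principle". Also: "In addition, per protocol (PP) and as-treated (AT) analyses will be performed as sensitivity analysis".
- Missing data, with the same wording in Retention: "non-adherence is no matter of discussion in our cohort".
- Group B: Control: the operation is the same except that no flap is made.

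**The concern.** The withdrawal text is about leaving the study, not only about leaving out the flap. Read literally, a flap-arm patient in whom the flap proves impossible may leave the trial, while a comparable control patient stays because nobody tries to make a flap in him. That is a post-randomisation decision, made with the arm known, on a criterion that exists in one arm.

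The primary outcome is collected months later by questionnaire and by contact with the outpatient urologist. A patient withdrawn in theatre therefore has no assured outcome. If such patients are missing from the comparison, the remaining flap arm is a selected group and randomisation no longer protects the result. Few events are expected, so a handful of patients can matter: 141 × 0.10 + 141 × 0.02 ≈ 17 under the planning assumptions, or 300 × 0.10 = 30 if both arms of 150 have a 10% risk.

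**Working it through.** **1. The sections side by side.** Randomization keeps and analyses all randomised patients, whereas Participant withdrawal lets some of them leave the study. Both cannot hold, so this contradiction is direct. The conflict with the intention-to-treat statement is indirect: that analysis can be carried out as promised only if the 6-month outcome of withdrawn patients is still collected, and the withdrawal text does not say that it is. The non-adherence sentences are loose wording that fits badly with a section describing an allocated flap that is not delivered.

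**2. Which arm is affected.** Controls have no planned flap, so the first example cannot occur there. The second, read in context, concerns the extra time for the flap step. The general safety clause covers both arms.

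**3. The plan's own figure.** Inputs from Sample size: 10% versus 2%, one-sided α 0.025, power 80%. With pooled variance under the null (mean risk 0.06):

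n = [1.960·√(2·0.06·0.94) + 0.842·√(0.10·0.90 + 0.02·0.98)]² / 0.08² ≈ 137.2, so 138 per arm.

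The stated 141 is within about 2% of this, with power 81.1%. Drop-out: 282 / 0.94 = 300, as stated. The planning figures are sound.

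**4. If the flap works as planned.** Let w be the share of the flap arm without a flap and r their risk. The article gives neither, so both are assumed. The intention-to-treat flap-arm risk is (1 − w)·2% + w·r. Excluding these patients leaves 2%, so the risk difference is overstated by w·(r − 2%). With r = 10%, the protocol's own no-flap risk, and 141 controls:

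| w | Flap-arm risk, all kept | Difference, all kept | Difference, excluded | Overstatement | Power kept / excluded |
|---|---|---|---|---|---|
| 5% | 2.4% | 7.6 points | 8.0 points | 0.4 | 75.6% / 79.8% |
| 10% | 2.8% | 7.2 points | 8.0 points | 0.8 | 69.7% / 78.4% |
| 15% | 3.2% | 6.8 points | 8.0 points | 1.2 | 63.4% / 76.8% |

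At r = 2% there is no overstatement. At r = 0% it reverses slightly, by 0.1 to 0.3 points for w = 5–15%.

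**5. If the flap has no effect.** Take 10% overall risk in both arms, 150 randomised per arm, a share f withdrawn from the flap arm, and k times the average risk in those withdrawn. The remaining flap-arm risk is (0.10 − f·k·0.10)/(1 − f). For example, f = 10% and k = 3 give 0.07/0.90 = 7.8%. Exact one-sided rejection rates of the Pearson test at 0.025, with 150 controls against 142 (f = 5%) or 135 (f = 10%) flap patients, are:

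| k | f = 5% | f = 10% |
|---|---|---|
| 0.5 | 2.1% | 1.7% |
| 1 | 2.5% | 2.4% |
| 2 | 3.5% | 4.9% |
| 3 | 4.9% | 9.3% |

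With nobody withdrawn the rate is 2.5%. With f = 2% and k = 2 it is 2.9%.

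**The case against.** The withdrawal section never says that these patients are removed from the analysis or that their data are discarded. Intention-to-treat is primary. Planning per-protocol and as-treated analyses shows that the authors foresaw patients not receiving their allocated procedure. Randomization says follow-up will be collected, and Retention promises every reasonable effort to follow each randomised patient. On this view, the withdrawal text means stopping the study intervention for safety while follow-up continues.

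Much of this stands. A reader might infer that the plan excludes these patients from the intention-to-treat set, or that it breaks three separate promises. The text supports one direct contradiction, one indirect conflict and some loose wording.

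A reader might also infer that the bias must favour the flap. That needs two things: the outcomes must be lost, and those withdrawn must be at higher risk than the flap patients who remain. The second is likely if the flap works, because those withdrawn did not receive it. If it has no effect, nothing in the article links difficult anatomy or operating time to lymphocele risk, and the bias may be nil or reversed. The Discussion calls the flap easy and quick, so the share affected may be small.

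What does not stand is the defence that the matter is only missing detail. The article contains two incompatible rules on whether a randomised patient can leave because the flap was not made, and the favourable reading depends on ignoring the words about leaving the study.

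**Conclusion.** The point holds as a contradiction to be reconciled before it affects who contributes to the confirmatory comparison. Followed as written, the withdrawal rule permits loss of patients that depends on the arm and leaves the primary analysis without assured outcomes for them.

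Its size is not known from the article. The overstatement of 0.4 to 1.2 points rests on assumed shares of 5–15% and on the protocol's own 10% risk without a flap. Under no effect, the range of 1.7% to 9.3% for a nominal 2.5% rests on assumed shares of 5–10% and on risks from half to three times the average; 9.3% is the extreme corner. All of these figures also assume that withdrawn patients are absent from the primary analysis, which the article neither states nor rules out. A certain bias towards the flap is therefore not established; the possibility of bias is.

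**What to change.** Reconcile Participant withdrawal with Randomization, Retention, Outcomes and Missing data. State that a patient in whom the flap is not created:

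- is recorded as allocated intervention not received, with the reason;
- stays in the study and has the same 6-month follow-up;
- is analysed in the allocated arm in the primary intention-to-treat analysis.

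State that only withdrawal of consent ends data collection. Correct the non-adherence sentences in Retention and Missing data. The planned per-protocol and as-treated analyses already address treatment received. The intraoperative decision about the flap is untouched.

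The cost is one paragraph plus two corrected sentences, with no extra patients or visits required by the wording itself. The effect estimate and power may be less favourable: under the assumptions above, power at 141 per arm is 75.6% with 5% of flaps not made, against 79.8% if those patients are excluded, and the gap widens as the share grows. The change should be made while patients are still in follow-up, because outcomes not collected may be unrecoverable.
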